### Prospective cohort study

Secondary outcomesThe sensitivity and specificity of new VOC sensing techniques (e.g. SIFT-MS and VOC sensors) for a diagnosis of asthma or transient wheeze in preschool children. Assessment at the start of the study in relation to the current gold standard in breath research (GC–MS) and at the age of 6 years in relation to the final diagnosis.Identification of other potential discriminating biological parameters (such as allergic sensitisation, immunological markers, epigenetics, transcriptomics, microbiome) between asthma, transient wheeze, and healthy controls, and the subsequent identification of underlying disease pathways and relation to the discriminative VOCs in exhaled breath. Assessment of data collected at the start of the study and at the end in relation to the final diagnosis at the age of 6 years.Identification of discriminative exhaled VOCs (based on GC-*tof*–MS analysis) between children with asthma, children with transient wheeze and healthy children. Assessment of data collected at the start of the study and at the end of the study in relation to the final diagnosis at the age of 6 years.

### Participant timeline

Both wheezing participants and healthy participants follow the same timeline (Fig. 1). Participants enrol in the study, after informed consent, at the age of 2 or 3 years old. At the baseline visit, the wheezing children that participate in the RCT will be randomised into either the intervention group or the usual care group. All children included in the study will perform the study-related procedures, including the breath test, at the baseline visit (see section “data collection” and Fig. 2). The children that will be allocated to the intervention arm of the RCT will receive their probability diagnosis and corresponding treatment advice within three months of the baseline visit. All children will be invited for the annual, study-related hospital visits until the age of 6. The performed study procedures at each visit are illustrated in Fig. 2. All parents will receive online questionnaires prior to the annual visit (a list of the questionnaires is provided in Fig. 3). Parents of children that participate in the RCT will also receive questionnaires on disease control and healthcare related expenditures with a 3-month interval. At the age of 6, a final diagnosis will be made based on respiratory symptoms, use of medication, and objective lung function measurements as reported previously [22].

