### Intervention

The intervention in the RCT consists of providing a probability diagnosis of either asthma or transient wheeze based on the earlier developed breath test of the ADEM study [22]. Based on this probability diagnosis, disease-specific recommendations on treatment and follow-up will be provided to the parents and treating physicians. At the start of the study, exhaled breath will be collected and sent to the central laboratory in the Maastricht UMC + for analysis on a GC-*tof*–MS. After analysis, the chromatogram is compared with our central database (based on the results of the ADEM study [22]) in order to determine whether the newly taken breath sample fits an asthmatic or a transient wheeze pattern of the selected VOCs. Parents and doctors of children allocated to the intervention group will receive the test result (probability diagnosis “asthma” or “transient wheeze”) within three months after the start of the study. In the children with a test result of “transient wheeze” in the intervention group, a restrictive policy towards use of asthma medication and referral to specialist care will be advised. In children with a test result of “asthma”, treatment with asthma medication according to international guidelines will be advised [29]. Parents and doctors of patients allocated to the usual care group will receive the test result at the end of the study at the age of 6 years. The management of preschool children with recurrent wheezing will be in accordance with national and international guidelines [29–31]. Both in the intervention and control group, treating doctors are at any time free to prescribe asthma medication, antibiotics or other drugs they judge as clinically necessary or meaningful.

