### Asthma or transient wheeze diagnosis at 6 years

The final diagnosis of transient wheeze or asthma will be made by two paediatric pulmonologists after the clinical visit at the age of 6 years. These paediatric pulmonologists will be blinded for the probability diagnosis (if applicable) of the participants. The asthma diagnostic algorithm for children as published by the ERS taskforce in 2021 [38] will be used to establish this final diagnosis. A diagnosis of asthma is made in children with symptoms of asthma when at least two out of the following objective test results are abnormal: spirometry, BDR or FeNO. With respect to spirometry, an FEV_1_/FVC ≤ the lower limit of normal (LLN) or ≤ 80%, ór an FEV_1_ ≤ LLN or ≤ 80% of predicted should be considered abnormal. If this is the case, BDR testing will be performed and an increase in FEV_1_ of more than 12% and/or more than 200 mL following an inhalation of 400 µg salbutamol is considered as an abnormal test result. A FeNO value ≥ 25 ppb should be considered as an abnormal test result. In those patients in which spirometry is normal, but FeNO concentration is higher than 25 ppb, a direct bronchial challenge test using methacholine will be performed. A provocative concentration of methacholine of ≤ 8 ml/mL that results in a 20% drop in FEV_1_ should be considered as a positive test.

Statistical methods

General descriptive statistics will be applied to describe the baseline characteristics. Table 2 depicts the different study groups in which the main statistical analyses will be performed.

**Table 2 Tab2:** outcome parameters and corresponding outcome measures and methods of analysis (see Fig. 5 for corresponding analysis groups)

Outcome	Analysis group	Outcome measure	Methods of analysis

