### Assessment accuracy of the VOC sensing techniques (GC-tof–MS, SIFT-MS)

The primary outcome of the prospective cohort study is assessed in two ways, namely by comparing the VOCs data of the two VOCs-sensing techniques (GC-*tof*–MS and SIFT-MS) at inclusion of all participating children (both wheezing preschool children and healthy controls) to the final diagnosis at six years of age, and by comparing the VOCs-data of the SIFT-MS at the baseline visit to the results of the gold standard (GC-*tof*–MS) at the baseline visit. The sensitivity, specificity, positive predictive value and negative predictive value for a diagnosis of asthma of the two different VOCs sensing techniques (GC-*tof*–MS and SIFT-MS) will be determined with corresponding 95% confidence intervals. Statistical analysis of the volatilome will be performed by current published standards on data analysis for VOCs analysis in breath [51]. The extensive VOCs data derived from the mass spectrometry analyses will be implemented in an algorithm by using mathematical models for analysis of sensor signals (for instance neuronal networks, random forest, support vector machine, or principle component analysis) as described previously [37].

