### Methodological issues

We decided to choose a RCT design for the following reasons: 1) to assess the full potential of the breath test in health gain and costs of care, a comparative study design is needed; 2) the breath test is not standard care yet; 3) in the usual care group, it is not unethical to provide the test result in a later phase, eventually all children/parents will benefit from the breath test result; 4) a safety rule will be applied in the usual care group so that parents/treating doctors can get the result of the breath test in an urgent situation (e.g. severe exacerbations, hospital admissions).

At first, we did not expect any problems with the feasibility of patient recruitment based on the high prevalence of children with asthma-like symptoms and our experiences during the first ADEM study. However, the outbreak of the SARS-CoV-2 pandemic in 2020 significantly affected the recruitment of participants. In the beginning of the pandemic, we were not allowed to perform research anymore by the Board of Directors of our hospitals. In a later phase, less preschool children with wheezing symptoms presented themselves at the outpatient clinic, emergency departments, and primary care facilities than before the crisis, which probably was the consequence of preventive measures taken (e.g. the lock-downs and temporary closure of schools and day-care facilities). As most of our patients were selected during and after the pandemic, this influenced intervention and control group equally.

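### The age-6 diagnosis used to judge the breath test is defined in two ways, and in the intervention arm the released result can influence it under either definition

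*Protocol article*

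**What the plan says.** **Two definitions of one endpoint.** Participant timeline states that at age 6 "a final diagnosis will be made based on respiratory symptoms, use of medication, and objective lung function measurements as reported previously [22". The section Asthma or transient wheeze diagnosis at 6 years states: "The asthma diagnostic algorithm for children as published by the ERS taskforce in 2021 [38] will be used to establish this final diagnosis". There, a child with asthma symptoms is diagnosed when "at least two out of the following objective test results are abnormal: spirometry, BDR or FeNO", with a methacholine challenge in some children. Use of medication is not among the criteria. The two sections differ in both content and cited source.

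**Who is analysed.** The section on accuracy of the VOC sensing techniques compares GC-tof-MS and SIFT-MS measured "at inclusion of all participating children (both wheezing preschool children and healthy controls) to the final diagnosis at six years of age". Study design places every RCT child in the cohort.

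**What the result does in one arm.** Under Intervention, parents and doctors in the intervention arm get the GC-tof-MS result within three months. After a transient wheeze result, "a restrictive policy towards use of asthma medication and referral to specialist care will be advised"; after an asthma result, "treatment with asthma medication according to international guidelines will be advised [29". Doctors in both arms may prescribe as they see fit. Usual-care families get the result at age 6, with an exception for urgent cases: Methodological issues says that "a safety rule will be applied in the usual care group so that parents/treating doctors can get the result of the breath test".

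**Blinding.** The section on the diagnosis at 6 years adds: "These paediatric pulmonologists will be blinded for the probability diagnosis (if applicable) of the participants".

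**The concern.** An accuracy estimate needs a reference standard that the index test does not influence. Here the index test is disclosed to half of the wheezing children, with treatment advice attached, some years before the reference standard is applied.

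- If medication use counts towards the diagnosis, a child told asthma is more likely to be medicated and therefore to be labelled asthma, and a child told transient wheeze is less likely to be. The test then contributes to its own confirmation.
- If only symptoms and objective tests count, treatment given because of the result may normalise them, so that a correct positive is recorded as not asthma.

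At stake are the sensitivity, specificity and predictive values of GC-tof-MS, which form part of the cohort study's primary outcome, and to a lesser degree those of SIFT-MS. As written, even the direction of the bias cannot be stated, because it depends on which section is followed.

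**Working it through.** **1. The two sections side by side.**

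| | Participant timeline | Diagnosis at 6 years |
|---|---|---|
| Source | earlier ADEM study [22] | ERS 2021 algorithm [38] |
| Symptoms | yes | yes |
| Use of medication | yes | no |
| Objective tests | lung function | at least two abnormal of spirometry, BDR, FeNO; methacholine in some |

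These cannot both be the rule for one child. The first admits incorporation of the index test. Treatment masking is possible under the second, and also under the first in so far as that uses symptoms and lung function.

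**2. Does the protocol itself expect treatment to move the reference tests?** Yes. The hypotheses section expects early diagnosis in children with asthma to give better control and improved lung function, and Outcomes compares spirometry at age 6 between arms. A quantity expected to respond to release of the result is not independent of that result.

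**3. Does blinding help?** It stops the pulmonologists from reading the result directly. It does not remove the result's trace in the medication history or in treated lung function.

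**4. Illustration of size.** The protocol gives no projected accuracy or sample size for this analysis, so there is no figure to reproduce. Inputs: asthma in about 30% of recurrent wheezers (Background); sensitivity 84% and specificity 82% (earlier ADEM study, in Background). The share *s* of children whose label moves is my assumption. For masking, read it as the excess over usual care.

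Per 100 wheezing children:
- TP = 30 × 0.84 = 25.2; FN = 4.8
- FP = 70 × 0.18 = 12.6; TN = 57.4
- Test positives = 37.8; PPV = 25.2 / 37.8 = 66.7%

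Relabelled false positives: PPV = (25.2 + 12.6*s*) / 37.8. Masked true positives: PPV = 25.2(1 − *s*) / 37.8. Pooled PPV is the mean of the arm value and 66.7%, since the arms are equal in size and have the same expected number of test positives.

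| *s* | Relabelled: intervention arm | pooled | Masked: intervention arm | pooled |
|---|---|---|---|---|
| 10% | 70.0% | 68.3% | 60.0% | 63.3% |
| 20% | 73.3% | 70.0% | 53.3% | 60.0% |
| 30% | 76.7% | 71.7% | 46.7% | 56.7% |

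Sensitivity/specificity, true values 84.0/82.0:
- Incorporation, with share *s* of both false positives and false negatives taking the test's label. Intervention arm: 86.0/83.6 at 10% and 89.6/87.0 at 30%. Pooled: 85.0/82.8 and 86.9/84.4.
- Masking. Intervention arm: 82.5/79.2 at 10% and 78.6/74.0 at 30%. Pooled: 83.3/80.6 and 81.7/77.8.

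**5. Precision.** With 10% dropout, 220 × 0.90 = 198 children, or 99 per arm. At 30%, that is about 59 asthma cases pooled and 30 in usual care. The half-width for sensitivity is 1.96 × √(0.84 × 0.16 / n): 9.4 points for n = 59 and 13.1 points for n = 30.

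**The case against.** The section on the diagnosis at 6 years is the dedicated one, with thresholds, two assessors and blinding; the timeline wording is a single closing sentence. If the dedicated section governs, medication is not a criterion and there is no self-confirmation. This stands, and it rules out a reading that a reader might infer, namely that the test simply grades itself. That follows only under the timeline definition. The dedicated section still leaves treatment masking, probably in the opposite direction.

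A reader might also infer that usual-care children give an uncontaminated estimate. The documents do not support this: they are managed by guideline and their doctors may prescribe asthma medication, so their tests can be altered by treatment too. What usual care lacks, unless the result is released early, is treatment driven by the result.

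The steering is advice only. The Pharmacotherapy section ties maintenance ICS to more severe symptoms and less controlled disease, and Methodological issues concedes that the contrast between arms may be small. So the share affected may be low, and large distortions of PPV should not be presented as expected.

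Finally, Table 2 assigns this analysis to group V, which is defined in a figure not shown, and a breakdown by arm may sit in a fuller document. That is fair: inclusion of both arms rests on the wording of the accuracy and Study design sections, and the absence of a table by arm is not in itself an error. Two conflicting reference standards, however, are not explained by condensation.

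**Conclusion.** The concern holds in limited form. The contradiction between the two definitions is plain in the text. Under either definition, release of the result in one arm can bias accuracy there and in the pooled estimate: upward through medication use as a criterion, likely downward through result-driven treatment.

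The size is not known. At an assumed 10% shift, pooled PPV moves from 67% to 68% or to 63%; at 10% to 30%, pooled sensitivity moves by about 1 to 3 points, less than its sampling half-width of about 9 points. These figures assume 30% prevalence, the earlier study's accuracy, and no early release in usual care.

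The effect is direct for GC-tof-MS, whose result is released, and indirect for SIFT-MS through its agreement with GC-tof-MS. The baseline comparison of SIFT-MS with GC-tof-MS and the RCT primary outcome (TRACK control) are not affected.

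**What to change.** 1. Reconcile Participant timeline with Asthma or transient wheeze diagnosis at 6 years, so that one reference standard applies. For the accuracy analysis, medication use should not be a criterion. This concerns the research endpoint only and leaves clinical care as it is.
2. Report sensitivity, specificity and predictive values among wheezing children by randomised arm, next to the pooled figure. Step 1 does not remove treatment masking. Because the breath sample is taken at baseline and arms are randomised, true accuracy should be the same in both arms apart from chance, so a difference between them is itself a check on bias.
3. Base the conclusion on accuracy on the usual-care arm, described as free of result-driven treatment rather than of all treatment.
4. Keep usual-care children whose result was released early in that estimate and flag them. Release is triggered by events such as severe exacerbation or admission, so dropping them would select on severity after baseline. Show the estimate without them only as a sensitivity analysis.

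The cost is a wording change and one stratified table. The leading estimate is less precise: the half-width for sensitivity is about 13 points instead of 9. If the bias is small, the pooled figure may lie closer to the truth on average, which is why it should stay in the table.

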**Fig. 1 Fig1:**
[figure not shown]
Flow of participants

**Fig. 2 Fig2:**
[figure not shown]
Schedule of enrolment, interventions, and assessments. * Children can enrol the study at 2 or 3 years of age. ** Only applicable for patients enrolling the study at 2 years of age_._ *** Applicable for patients enrolling the study at 2 or 3 years of age. **** Applicable to those patients randomised into the treatment group. PBMC Peripheral blood mononuclear cells

**Fig. 3 Fig3:**
[figure not shown]
Schedule of questionnaires. *QoL* Quality of life. * Applicable for children enrolling the study at 2 or 3 years of age

### Sample size

*Randomised controlled trial* With a presumed percentage of well-controlled preschool children with asthma-like symptoms of 20% in the usual care group (based on reference [32, 33]), and of 40% in the intervention group, 91 patients in both groups are needed to detect this difference with an alpha of 0.05 and a power of 80%. Taking a dropout rate of 10% into account, we aim to include a total number of 220 preschool children with asthma-like symptoms.

*Prospective cohort study* For studies assessing the relationship between microbiome, transcriptomics, epigenetics, and atopic outcomes like asthma, a sample size of 70–80 is considered adequate [34, 35].

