
### Objectives of the new study: the ADEM2 study

The previous ADEM study generated a lot of insight in the diagnostic potential of VOC patterns in exhaled breath with respect to an early diagnosis of asthma, and in multiple potential underlying pathophysiological mechanisms leading to the development of asthma. However, since then, many new questions arose. For example with regards to the feasibility of bringing the assessment of VOCs in exhaled breath into daily clinical practice, and with respect to the impact an early diagnosis of asthma will have on wheezing preschool children and their parents. Also, recent developments in the evolving field of multi-omics generated new approaches to investigate the early pathogenesis of asthma. Therefore, a new randomised controlled trial and prospective study in wheezing preschool children was designed, the ADEM2 study.

The primary objective of the ADEM2 study is to prove health gain and reduction in costs by application of a point-of-care (POC) breath test for an early asthma diagnosis in preschool children. A multicentre randomised controlled trial (RCT) in 220 wheezing preschool children will be performed. Children will be randomised into an intervention group (*n* = 110) in which the doctors and parents will be informed about the predicted asthma diagnosis provided by the breath test, or into a usual care group (*n* = 110) in which all parties are masked for the predicted diagnosis. The second objective is to further develop and validate a reliable, non-invasive point-of-care breath test. In a prospective observational study we will assess feasibility, accuracy and reproducibility of the innovative VOC techniques (e.g. SIFT-MS and VOC sensors) in comparison with the gold standard breath test (GC-tof–MS), for an early asthma diagnosis in wheezing preschool children. The third and final objective of the ADEM2 project is to combine metabolomic, immunological, (epi)genomic, transcriptomic, and microbiome data to unravel potential important pathways for asthma development. Moreover, the utility of predictive, multi-omic testing of childhood asthma in wheezing pre-school children will be explored. This knowledge can offer clues for novel diagnostic tests and proper or even revised treatment (e.g. microbiota-based therapy) in wheezing children.

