### Allocation and blinding

The wheezing preschool children that participate in the RCT will be randomly assigned (1:1), with a secure computer-generated block randomisation procedure (block size of 6), into a usual care group and an intervention group. The randomisation will be organised by the Clinical Trial Centre Maastricht (CTCM) and MEMIC (centre for data and information management at the Faculty of Health, Medicine and Life Sciences of Maastricht University and MUMC +). Randomisation is stratified per measurement centre. The participants, treating physicians and the researchers or research assistants involved in conducting the baseline visit are not blinded to the results of the randomization procedure. The assessment of the primary outcomes and secondary outcomes after one year and at the end of the study will be done by researches who were not involved in the recruitment and randomization procedures. These researchers will be blinded towards the allocation in randomisation group and (final) diagnosis of the participants.

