A cost-effectiveness analysis will be performed from a societal and healthcare perspective with a time horizon of 2 years. Incremental cost-effectiveness ratios will be calculated as societal cost per QALY (societal perspective) and health care cost per additional child with control of asthma-like symptoms (healthcare perspective). Standard sensitivity- and bootstrap analysis will be performed to address uncertainty regarding costs and cost-effectiveness outcomes. Cost-effectiveness acceptability curves will be constructed reflecting the probability that the diagnostic breath test is cost-effective for a range of threshold values. Costs and effects after one year will be discounted at 4.0% and 1.5% respectively, according to the Dutch guidelines for health economic evaluation [45, 48].

All outcome parameters and corresponding outcome measures and methods of analysis are listed in Table 2. The large number of patients (*n* = 220) allows better representation of specific subgroups of specific age, background (primary or secondary/tertiary care), genetic predisposition, and geographic area. All these parameters will be measured and included in the multivariable analysis in order to assess possible influences on outcome. Intention-to-treat analyses will be applied. We will execute two subgroup analyses: one for age and one for level of care (first-line versus secondary/tertiary care). Two-sided *p*-values < 0.05 (with correction for multiple testing) will be regarded as statistical significant.

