We do not expect problems with drop-outs during the study because the breath test and the questionnaires are non-invasive, and the parents, children and treating doctors are highly motivated. Moreover, the ADEM study had a comparable design and burden with only 2% loss to follow-up [22]. We will limit the expectations of the parents and health-care workers and emphasize that the breath test has not a 100% reliability. We will keep the contrast between intervention and control group as large as possible by continuous training and instruction of treating doctors and centres. One potential pitfall of the RCT may be a small contrast between intervention and usual care group. Doctors are not used to get a reliable diagnosis of asthma in pre-schoolers and may not act appropriately on the result of the breath test. Moreover, we cannot exclude that at least some children with transient wheeze may benefit from treatment with ICS, which may diminish the contrast between intervention and control group as well.

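### The target of 220 does not follow from 91 per group and 10% dropout, which give 204; the excess is on the safe side

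*Protocol article*

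**What the plan says.** The Sample size section of the protocol article assumes a "presumed percentage of well-controlled preschool children with asthma-like symptoms of 20% in the usual care group" and "of 40% in the intervention group". From these it states that "91 patients in both groups are needed to detect this difference with an alpha of 0.05 and a power of 80" (per cent). The next sentence gives the target: "Taking a dropout rate of 10% into account, we aim to include a total number of 220 preschool children with asthma-like symptoms".

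The section on the objectives of the study repeats the total: "A multicentre randomised controlled trial (RCT) in 220 wheezing preschool children will be performed", with 110 in each group. Under Allocation and blinding, children "will be randomly assigned (1:1" to the two groups. The statistical methods give the sidedness: "Two-sided *p*-values < 0.05 (with correction for multiple testing").

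The Sample size section gives no other allowance as a reason for going from 182 to 220: no rounding margin, and nothing for clustering, multiplicity or subgroups.

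**The concern.** The section prints all its inputs and its result together, so a reader can check the chain, and the last link fails. Twice 91 is 182, and a 10% loss does not raise 182 to 220.

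The enrolment target is the figure that an ethics committee approves and against which recruitment is judged. The article's section on methodological issues reports that the pandemic markedly affected recruitment. If enrolment fell short, the question would be how many children are enough. Taken at face value, the text says that 220 are needed if 10% are lost. By the document's own inputs that number is 204, and 220 allows for a considerably larger loss than the 10% stated.

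**Working it through.** **Inputs** (Sample size, unless noted): p1 = 0.20, p2 = 0.40, difference 0.20, mean proportion 0.30; alpha 0.05, two-sided (statistical methods); power 80%; allocation 1:1 (Allocation and blinding); dropout 10%; total 220.

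**Step 1: reproduce the 91 per group.**

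Pooled two-proportion formula:

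n = [1.960 × √(2 × 0.30 × 0.70) + 0.842 × √(0.20 × 0.80 + 0.40 × 0.60)]² / 0.20² = 81.2

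With the continuity correction:

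n' = (n/4) × [1 + √(1 + 4/(n × 0.20))]² = (81.2/4) × [1 + √(1 + 4/16.24)]² = 90.95, so 91.

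This matches the plan. Other choices do not: 82 without the correction, 79 with unpooled variance, 81 with the arcsine method, and 64 or 74 (without or with correction) if one-sided. At 91 per group, power is 80.0% with the correction and 80.8% by Fisher's exact test. The first step is therefore sound.

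**Step 2: add 10% dropout.**

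| Convention | Calculation | Total |
|---|---|---|
| Divide per group | 91/0.9 = 101.1, so 102 | 204 |
| Divide the total | 182/0.9 = 202.2, so 203 | 203 |
| Multiply per group | 91 × 1.1 = 100.1, so 101 | 202 |
| Multiply the total | 182 × 1.1 = 200.2, so 201 | 201 |

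No convention comes near 220. The gap from 204 is 220 − 204 = 16 children, and 16/204 = 7.8%. Filling randomisation blocks does not explain it either: the block size is 6, and 204 = 34 × 6 already.

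**Step 3: what 220 corresponds to.**

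- Dropout that leaves 91 of 110 per group: 1 − 91/110 = 17.3%.
- As a simple multiplier: 220/182 = 1.209. Multiplying 91 by 1.2 gives 109.2, which rounds up to 110 per group.

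**Step 4: power if 220 are randomised and 10% are lost.**

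Completers: 110 × 0.9 = 99 per group. By the same continuity-corrected calculation:

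z = [0.20 − 1/99 − 1.960 × √(0.42/99)] / √(0.40/99) = (0.1899 − 0.1277)/0.0636 = 0.98, so power = 83.6%.

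Fisher's exact test gives 84.2%, and the uncorrected comparison gives 87.2%.

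**The case against.** The strongest defence is that nothing in the trial is weakened. The target exceeds what is needed, the wording is that of an aim, and a sponsor may round up or keep a margin for reasons set out in a full protocol that is not shown. The statistical methods also mention that the large number of patients helps to represent subgroups. That is a fair reason not to touch enrolment. It does not repair the sentence: the Sample size section attributes 220 to the 10% dropout, and the subgroup remark is not offered as a derivation.

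A different route to 220 exists. Two-sided alpha 0.025 without continuity correction needs 99 per group, and 99/0.9 = 110. But the section states alpha 0.05 and 91 per group, so this is conjecture and cannot be the printed derivation.

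Three stronger readings are tempting, and the document supports none of them.

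- **That the stated 80% power is wrong.** The section ties 80% to 91 per group, where it is right. It claims no power for 220 randomised or for 99 completers. Exceeding a planning minimum contradicts nothing.
- **That the dropout assumptions conflict.** The section on methodological issues says that "the ADEM study had a comparable design and burden with only 2% loss to follow-up". Planning for 10% when an earlier study lost 2% is ordinary prudence.
- **That the tolerated dropout cannot be known.** It follows from two printed numbers, as Step 3 shows. The text does not say it, but it can be worked out.

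**Conclusion.** The point holds as an arithmetic discrepancy in one step. From 91 per group and 10% dropout the total is 204 (201 to 203 by other conventions). The stated 220 is 16 above 204 and corresponds to about 17% dropout. The 91 per group at 80% power is correct.

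The direction is conservative. A reader might infer from a faulty sample-size paragraph that the trial is underpowered. It is not, for 20% versus 40%: at 10% dropout power is about 84%, and 91 per group are kept up to 17.3% loss.

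These figures rest on the section's own control and intervention rates, two-sided alpha 0.05, equal groups, equal dropout in both groups, and the continuity-corrected two-proportion calculation that reproduces 91. They describe that planning calculation only. Table 2 and the section on differences in asthma control list an unpaired t-test or Mann-Whitney test for the TRACK outcome, so the power figure should not be read as the power of those tests.

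**What to change.** Restate the last sentence of the randomised-trial paragraph under Sample size in one of two ways:

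- 204 children are needed with 10% dropout; the target is set at 220, which keeps 91 per group up to about 17% dropout. If there was a reason for the larger target, add it.
- 220 children are randomised; with 10% dropout 99 per group remain, giving about 84% power for 20% versus 40% by the same continuity-corrected two-proportion calculation that gave 91.

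The first is the simpler. It does not present 17% as an assumption that was made in advance, only as the loss the target can absorb. If the second is used, tie the power to the planning calculation as worded, because the listed tests for the TRACK outcome are different.

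The cost is one sentence. Enrolment, design and analysis do not change, and the remark on 2% loss in the earlier study can stay as it is.
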